### Indigenous Governance

A Research Governance Group to support and guide the research comprises Indigenous environmental health experts, a Department of Communities (Housing) representative, an Indigenous policy expert, and an Indigenous community advocate. These representatives live in the Midwest, Kimberley, Goldfields, and Perth or Peel regions of Western Australia. Reciprocity is reflected in this Research Governance Group, whose membership has been determined and agreed in consultation with different communities involved in the research. Roles of the group are to identify potential benefits and implications related to the values and aspirations of the community; avert any unintended consequences; provide advice on cultural security issues, barriers and enablers, data sovereignty and dissemination, and food security issues relevant to remote communities; and contribute to knowledge transfer strategies.

### Community Engagement

The established relationships developed with each community through the #endingtrachoma project inform and support this research methodology. All data collection is informed by community aspirations to ensure food security. Permission to enter each community will be obtained prior to, and with an invitation from, the community chairperson of each community. Posters describing the study will be displayed in the community store, at the health clinic and art center, to advise community members of the date and purpose of the visit. Visits will coincide with the #endingtrachoma project visits.

### Mixed Methods Approach

#### Overview

This mixed method study involves (1) an in-home digital healthy home kitchen functionality audit and food security check incorporating digital images where appropriate (n=197), (2) yarns (short interviews) with tenants (n=100) exploring their perspectives on food security issues and preferred kitchen design, and (3) store pricing survey using the digital Healthy Diets ASAP (Australian Standardized Affordability and Price) app [63].

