**Methods:**

The mixed methods eHealth study includes 3 approaches. The internal environment is assessed via an in-house audit of facilities used to prepare, store, and cook food to maintain Healthy Living Principle 4 using a customized digital app and a 5-minute face-to-face yarn with tenants (n=130). This provides lived experience perspectives to inform housing and store pricing policy recommendations. The external environment assesses retail practices and food item (n=97) and sanitation product (n=28) prices in remote community stores, extending Healthy Diets ASAP (Australian Standardized Affordability and Price) to compare the mean price per product, the whole diet, and sanitation goods with the nearest town and capital city. Descriptive statistics and frequencies will be reported for the audits, and thematic analysis of the interviews will be undertaken.

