#### Internal Environment—Community Housing and Kitchen Audits

##### Overview

Over 12 months, 197 households across 19 communities will be visited. No private or state-owned houses will be audited. Some tenants will be away, and not all houses will permit entry, and based on our previous experience, a 70% participation rate is achievable. The long-term engagement with the community and the support of EHP facilitate this. Nonparticipation is predominantly due to cultural reasons such as death in the family and lore. Where entry is allowed, the food security researchers will conduct the kitchen audit and a face-to-face yarn with an adult tenant (n=100). Researchers on this food security project have been working on the #endingtrachoma project for the past 5 years and have extensive knowledge of the remote communities involved and have built robust and genuine relationships with the community leaders, local service providers, and many of the community members.

In each community, an Indigenous EHP team member will lead the conversation to gain permission to enter each community-managed house. The EHPs are local people who live and work in remote communities. They hold a very strong understanding of the communities. With permission, they will introduce the food security researchers to the tenant, who will invite the householder to participate in the research. A project information sheet will be provided or read out if required, and signed consent obtained with the option to opt out.

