## Results

The project was funded in November 2024, and data collection commenced in February 2025. Accessing remote communities is challenging due to distance, a lack of transport options, weather restrictions, and costs. At the time of publishing, 10 remote communities had been accessed, with 47 yarns being recorded, 61 healthy kitchen audits being completed, and 8 remote store prices being analyzed. The final data collection is due to be completed by June 2026, and results will be analyzed by November 2026.

There are several expected outcomes associated with this research. The internal environmental health data collection will provide baseline information on the functionality of kitchens in the very remote communities that participate in this research. Broadly, the expected outcomes reported are shown in Textbox 1.

Expected outcomes of the benchmarking environmental health influences on food security in very remote Indigenous communities in Western Australia.

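### The kitchen audit is given as n=197, but that is the number of households to be visited; at the stated 70% participation about 138 audits are expected, and the yarn sample size is given as both 130 and 100

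*Protocol article*

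**What the plan says.** Three places in the protocol article size the in-home component.

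- **Methods, Mixed Methods Approach, Overview.** The first component is "an in-home digital healthy home kitchen functionality audit and food security check incorporating digital images where appropriate (n=197"; the second is "yarns (short interviews) with tenants (n=100".
- **Internal Environment—Community Housing and Kitchen Audits, Overview.** "Over 12 months, 197 households across 19 communities will be visited". The text continues: "Some tenants will be away, and not all houses will permit entry, and based on our previous experience, a 70% participation rate is achievable". Where a house can be entered, "the food security researchers will conduct the kitchen audit and a face-to-face yarn with an adult tenant (n=100".
- **Abstract, Methods.** The in-house audit is described together with "a 5-minute face-to-face yarn with tenants (n=130".

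The Results section reports progress from 10 communities: "47 yarns being recorded, 61 healthy kitchen audits being completed, and 8 remote store prices being analyzed". Textbox 1 lists the numbers of audits attempted and completed as project outcomes, and completed audits by community. No section states an expected number of completed audits.

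**The concern.** One figure, 197, does two jobs. In one section it counts audits; in the next it counts households to be visited, some of which the plan expects not to enter. Both can be true only if every household takes part, and the plan says that will not happen. The yarn component has two sizes, depending on whether one reads the Abstract or the Methods.

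This is a benchmarking study whose kitchen results are descriptive statistics over audited houses, so the number of completed audits is the denominator of those results. A reader who takes 197 as that denominator overstates what the design is set up to deliver. The findings are meant for communities and government agencies to use in advocacy, where an avoidable mismatch between stated and achieved numbers is easy to challenge. The Introduction also names low participation in food security research in remote Western Australia as a gap the study intends to fill. Presenting households approached as households audited hides the quantity that would show whether it did.

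**Working it through.** **Inputs, all from the protocol article**

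- Stated audits: 197 (Mixed Methods Approach, Overview).
- Households to be visited: 197 in 19 communities (Internal Environment, Overview).
- Participation: 70% (same section).
- Yarns: 130 (Abstract); 100 (both Methods overviews).
- Progress: 61 audits and 47 yarns from 10 communities (Results).

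**1. Can the stated audit number be reproduced?**

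Expected audits = households visited x participation = 197 x 0.70 = 137.9, about 138. This does not reproduce 197.

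Shortfall: 197 − 138 = 59 houses; 59/197 = 30%.

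**2. Which meaning of 197 fits the plan?**

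- As households approached: 138/0.70 = 197.1, which agrees with 197.
- As completed audits: 197/0.70 = 281.4, so about 281 households would have to be visited. No such number is planned.

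The figure therefore fits as the number approached.

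**3. Are the two yarn sizes reconcilable?**

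| Stated yarns | Share of 197 approached | Share of about 138 audits |
|---|---|---|
| 130 | 130/197 = 66% | 130/138 = 94% |
| 100 | 100/197 = 51% | 100/138 = 72% |

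Neither figure is derived in the text, and no sentence links them. They differ by 30.

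**4. Is 100 yarns compatible with about 138 audits?**

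So far there have been 47/61 = 0.77 yarns per audit. Applied to 138 audits, 0.77 x 138 gives about 106, close to 100. The yarn fault is therefore the disagreement between 130 and 100. The figure of 100 is not itself at odds with the audits.

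**The case against.** The best case for the plan is that the n=197 is loose shorthand which the following section explains: it says 197 households are visited, that some will not be entered, and that 70% is achievable. The figure does not appear in the Abstract. The Abstract's 130 closes a phrase covering both audit and yarn; read as the size of both, it is 66% of 197, near the 70% expectation. No hypothesis test, precision target or decision rule depends on these numbers, and the sample is purposive and declared not generalizable. Textbox 1 already plans to count attempted and completed audits, from which participation can be derived.

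Much of this stands. It limits the matter to stated sample sizes and leaves the analysis untouched. It does not remove the contradiction. The overview attaches n=197 to the audit, and a reader must rework it from another section to reach the expected yield, which is never stated. Reading 130 as covering both components still leaves it in conflict with 197 audits and 100 yarns.

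Three stronger readings are tempting, and the document does not support them.

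- **That about 138 yarns are implied because audit and yarn both follow entry.** That sentence itself carries n=100. Under Yarning, tenants are invited and may prefer a group yarn, and consent includes an option to opt out. Yarns need not equal audits.
- **That progress shows the targets will be missed.** Scaling by community gives 61/10 x 19 = 115.9 audits and 47/10 x 19 = 89.3 yarns. This assumes the nine remaining communities yield as much as the first ten and that the first ten are finished. Houses per community are not given. Setting and Recruitment says houses are revisited every 4 months, and Community Engagement says study visits coincide with those visits. An even spread of houses would put 197 x 10/19 = 103.7 in the first ten communities and participation at 61/103.7 = 59%. If those communities held 61/0.70, about 87 houses, participation would be 70%, and nothing excludes that.
- **That precision is materially lost.** Simple-random-sampling half-widths at 50% prevalence, 1.96 x √(0.25/n), are 7.0 points at n=197 and 8.3 at n=138. They ignore clustering and the finite number of houses, and do not describe a purposive descriptive sample.

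**Conclusion.** The concern holds for two stated sample sizes. First, 197 is the number of households to be visited; the design's own expected number of audits is about 138, 30% below the n attached to the audit. This rests only on the plan's 70% participation and on audits taking place where entry is allowed. Second, the yarn size is 130 in one place and 100 in two others, with no reconciliation; that needs no assumption.

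It goes no further. The interim counts neither confirm nor refute either target. A reader might infer that the design cannot reach its numbers, or that the kitchen results will be biased or mis-analysed; nothing in the document shows this. Results calculated over completed audits would be unaffected by the wording, provided that denominator is made explicit.

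**What to change.** 1. In Methods, Mixed Methods Approach, Overview, replace n=197 with: 197 households approached; about 138 audits expected at 70% participation.
2. State one yarn target in the Abstract, the Mixed Methods Approach overview and the Internal Environment overview. A target of 100 is compatible with about 138 audits, since not every audited house need give a yarn.
3. Give kitchen results with completed audits as the denominator, and show the number of households approached beside it. The attempted and completed counts in Textbox 1 already supply most of this.
4. Do not write a projection from the interim counts into the plan.

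The cost is wording in three places. The stated audit size becomes smaller; no extra recruitment, visits or analysis are needed. Data collection runs to June 2026, so the correction can be made before results are reported.

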#### Internal Environment—Community Housing and Kitchen Audits

##### Overview

Over 12 months, 197 households across 19 communities will be visited. No private or state-owned houses will be audited. Some tenants will be away, and not all houses will permit entry, and based on our previous experience, a 70% participation rate is achievable. The long-term engagement with the community and the support of EHP facilitate this. Nonparticipation is predominantly due to cultural reasons such as death in the family and lore. Where entry is allowed, the food security researchers will conduct the kitchen audit and a face-to-face yarn with an adult tenant (n=100). Researchers on this food security project have been working on the #endingtrachoma project for the past 5 years and have extensive knowledge of the remote communities involved and have built robust and genuine relationships with the community leaders, local service providers, and many of the community members.

In each community, an Indigenous EHP team member will lead the conversation to gain permission to enter each community-managed house. The EHPs are local people who live and work in remote communities. They hold a very strong understanding of the communities. With permission, they will introduce the food security researchers to the tenant, who will invite the householder to participate in the research. A project information sheet will be provided or read out if required, and signed consent obtained with the option to opt out.

##### Kitchen Audit

The food security researchers will conduct a digital healthy home kitchen functionality audit. This audit is based on the SafetyCulture Healthy Home app used in the #endingtrachoma project and is consistent with the HLP 4 criteria [44,64]. It will be a new tool developed for this research. Knowledge and experience from 5 years of completing the healthy home audits via the SafetyCulture app will guide the design of the kitchen app. The audit will assess cleanliness and functionality for food storage, preparation, and cooking in household kitchens. The audit captures issues associated with kitchen functionality, availability and state of cooking appliances, presence of cleaning and hygiene products, and kitchen requirements to prevent pests and vermin entering the house. The taps in the kitchen are turned on to ensure that both hot and cold water are available to the house. These details of the audit have been included as examples of auditing practices. The 64-item audit assesses evidence of pests, mold, waste disposal, basic utilities, kitchen, plumbing and electrical appliances (eg, oven, stove, refrigerator, freezer, ventilation, and other white goods), kitchen benches, cupboards and pantry, cooking utensils, cleaning and hygiene products, windows, and doors. A question is asked within the app to identify the number of people who slept in the house on the previous night. This provides an indication of crowding issues. Digital photographs are included in the audit data collection. The #endingtrachoma team will provide emergency plumbing fixes throughout the house, including the kitchen, as required. If the repair is unable to be carried out, the fault will be reported to the housing provider. A kitchen kit comprising household kitchen hygiene products and a small plunger will be offered to each house where a complete audit has occurred to thank tenants for their participation.

##### Yarning

Yarning is a conversational process that involves the sharing of stories and the development of knowledge and reflects Indigenous people’s emphasis on oral traditions [65,66]. Yarning can involve a range of fluid narrative strategies such as anecdotes, stories, and personal experiences [67]. Burke et al [68] suggest that this fluid style of questioning is more likely to reflect Indigenous peoples’ perspectives, as it is less confrontational. It is considered to be one of the most appropriate research methodologies to determine Australian Indigenous community members’ perceptions of their health needs and is considered culturally safe if conducted in a way that is respectful, cooperative, and supports cultural practice [68,69]. Yarning has been shown to foster connection, establish trust, and enable researchers to explore topics in greater detail [70]. Tenants will be invited to have a one-to-one yarn, or if preferred, a group yarn, about what their kitchen might look like if they had the opportunity to design it and how they like to prepare the food they eat. The yarns will occur inside the homes while the kitchen audit and healthy home audits are being conducted. In some cases, the Indigenous EHP will instigate the yarn, and in other cases, where the EHP is busy fixing a plumbing issue, the yarn will be led by the research team (non-Indigenous). Either way, an Indigenous person will always be in the house when the yarns occur. The yarning question will encourage flexibility and disclosure. The participant will be asked to choose where they would like to have the yarn, and a Voice Memos mobile telephone audio recording app will be used to record the yarn.

#### External Environment—Community Store Pricing Audits

As food insecurity is driven by a complex range of factors, such as inadequate income to support meal planning and food purchases, food prices, poor access to safe storage and cooking facilities, limited transport options to access stores, and poor access to fresh and nutritious foods, focusing on the community store environment and pricing policies is a critical component of this study. A recommendation from the 2009 Parliamentary Inquiry into remote Aboriginal and Torres Strait Islander community stores [28] was a requirement to display pricing. However, under Australian Consumer Law, there is no specific legal requirement for stores with less than 1000 m^2^ of floor space to display prices [71].

The Healthy Diets ASAP app [63] will be used to audit prices of food products (n=76) in each of the 15 independent stores located within the 19 remote Indigenous communities, along with audits in the 6 nearest regional towns and the capital city, Perth, for comparison. The digital survey tool has been tailored to assess the food affordability component of food security in remote Indigenous communities [72]. This Healthy Diets ASAP method allows the “assessment of price, price differential and affordability of healthy (recommended) and current (unhealthy) diets of Aboriginal and Torres Strait Islander people living in different locations with other population groups in Australia” [72]. Observation of evidence of pricing policies will also be undertaken, including the presence or absence of prices on shelves for all products. Photographs of food and hygiene items will be taken where appropriate and will confirm the presence of shelf pricing. Hygiene products (n=28) that are required to keep kitchens and work areas clean and support handwashing (eg, soap and detergent) will also be priced. Data will be collected in-store using an iPad and uploaded via a web-based portal. Permission will be sought from each community store manager to undertake the pricing audit, and entry to communities must be granted by the community chief executive officer (CEO) prior to each visit.

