**Objective:**

This study aims to benchmark environmental health food security risk factors impacting 19 very remote Indigenous communities in Western Australia. Specific objectives include using digital apps (1) to assess the appropriateness and suitability of kitchens in houses (internal environment), (2) to assess the affordability of food and sanitary goods (external environment) compared with the nearest town and capital city, and (3) to identify residents’ perceptions of appropriate kitchens.

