**Results:**

Tenant interviews and data collection for the in-house and retail audits across the 19 communities will be undertaken by mid-2026, and the analysis will be completed by the end of 2026. Findings will be collated and triangulated to provide benchmark data for environmental health determinants of food security in very remote Western Australian communities. Preliminary findings will be shared with each community to support their advocacy, policy, and practices for timely maintenance of homes, suitable kitchen design, and store retail practices.

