### Environmental Determinants of Food Insecurity—Food Access and Affordability

In 2024, over 200 food stores service remote Indigenous communities across Australia, providing 90% to 95% of the food consumed, and traditional foods contribute only a small, but important, supplement to people’s dietary intake [19]. Community stores are either managed by store management companies, where external agencies maintain control, or are community-owned and managed. Often, community-owned stores serve smaller populations and have less purchasing power or ability to buy in bulk. Residents in communities with no store are required to travel many hours on unsealed or seasonally inaccessible roads to a retail provider in a regional town to purchase their food.

Restricted access to and the limited choice for a variety of healthy foods in remote stores have negatively impacted the dietary habits and health of Indigenous people living in remote communities [27]. The National Indigenous Australians Agency (2025), following consultation across these areas, reported that people in these communities often relied on “cheaper convenience foods, which are often nutrient-poor and higher in calories,” as they were more affordable in these community stores [19]. Regular consumption of this food-insecure dietary pattern increases the risk of diet-related disease among Aboriginal and Torres Strait Islander Australians including diabetes, oral health issues, kidney disease, cardiovascular disease, and some cancers [19].

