### Setting and Recruitment

This mixed methods study will be undertaken in 19 very remote Indigenous communities across 4 regions of Western Australia: the Pilbara, Goldfields, Midwest, and Central Desert regions. Very remote areas, as classified by the Australian Statistical Geography Standard-Remoteness Area classification, rely on the Accessibility/Remoteness Index of Australia, measuring the relative geographic access to services. Very remote areas [58] represent high levels of disadvantage based on the Australian Bureau of Statistics’ Index of Relative Socio-Economic Disadvantage for Areas [59]. People living in very remote areas are 58% more likely to speak an Australian Indigenous language at home [60]. The research will be undertaken alongside Curtin University’s #endingtrachoma project, which has established relationships with these communities. The #endingtrachoma project has been servicing Western Australia’s remote communities since 2019 and is delivered in partnership with Indigenous environmental health practitioners (EHPs) in each community. The project facilitates an approach led by the community including in-home bathroom and laundry assessments and emergency maintenance [61]. The purposeful sample has been identified as “trachoma at risk” communities based on annual trachoma screening that identifies active trachoma prevalence of 5% or greater among Aboriginal and Torres Strait Islander children aged 5-9 years in the last 5 years [62]. #endingtrachoma has been building the capacity of local Indigenous EHPs to enter homes, identify and audit trachoma risk factors (eg, ability to wash), fix minor plumbing issues, yarn with tenants about hygiene, and provide hygiene resources. The #endingtrachoma project revisits each house every 4 months. An important component of the project is to transfer the auditing skills to the EHPs who service these communities. These EHPs are contracted to visit these communities every 4 months and collect data using the mobile app. This research will build on this to include environmental health and food security risks.

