### Strengths and Limitations

Several factors may influence this research, including geographic isolation and distance to travel to each community, climatic conditions and weather events (eg, floods and fires), and cultural practices (eg, Lore and Sorry Time), which dictate periods when communities are not accessible. Knowledge formed through involvement with the #endingtrachoma project will inform the most appropriate seasons and times to visit communities. Communities will not be entered without explicit approval from the community CEO. Different geographic locations and cultural practices mean that the results of the kitchen audit and yarns are not generalizable to other communities or populations.

There are limitations related to the choice of food price measure, as the purpose of the Healthy Diets ASAP is to compare the price of a healthy diet versus an unhealthy dietary pattern and does not measure a wider selection of food products available, for example, where dietary preferences differ between communities. Time limitations in the current methodology would not permit the auditing of more food items or the quality of food, which is an issue impacting food security in remote communities.

The strength of this study is the research that is to be conducted in 4 remote regions in Western Australia and 19 of the 46 very remote stores in Western Australia. The benchmarking and methodology established may be used to further research in other communities. A further strength is that the store price benchmarking results will be compared within regions and to the nearest town and urban center to highlight food insecurity and high prices as potentially significant issues in remote communities. Being able to work alongside a well-known and experienced existing project that has strong connections into the communities to be visited and working with local Indigenous people in their communities are also strengths of this study.

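### The Methods audit 15 stores but the Discussion claims 19 of 46, and on the Methods count at least 4 of the 19 communities have no audited store for the promised price comparison

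*Protocol article*

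**What the plan says.** The aim in the Abstract is to "benchmark environmental health food security risk factors impacting 19 very remote Indigenous communities in Western Australia", and objective 2 compares affordability with the nearest town and the capital city. The setting is given as 19 communities in 4 regions. On how many stores supply the prices, the article differs from place to place:

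- Methods, Community Store Pricing Audits: prices are audited "in each of the 15 independent stores located within the 19 remote Indigenous communities". Six regional towns and Perth serve as comparators.
- Strengths and Limitations: the study is said to cover "19 of the 46 very remote stores in Western Australia".
- Abstract, Results: "data collection for the in-house and retail audits across the 19 communities will be undertaken by mid-2026".

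Two-Way Sharing of Information says that results go back to each community. They include average price and share of income needed for a healthy and an unhealthy diet at three levels: community store, regional town store and capital city. The external-audit outcomes in Textbox 1 are mean (SD) costs, affordability, and cost comparison with the nearest town and the capital.

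The Introduction accepts that some communities have no store: "Residents in communities with no store are required to travel many hours on unsealed or seasonally inaccessible roads to a retail provider", which it places in a regional town. It also describes two kinds of community store, those run by management companies and those owned and managed by the community. It does not say which of these the word *independent* in the Methods refers to.

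**The concern.** In a benchmarking study, the number of stores is the sample size for every store outcome, and the share of all very remote stores is the claim to coverage. Here the Methods and the Discussion give different numbers for the first and so imply different values for the second. A report that quotes the Discussion figure would overstate what the Methods plan to measure.

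There is also a second-order problem. With fewer audited stores than communities, some communities have no local price to put into the comparison that all are promised. The article gives no rule for what stands in its place, so the denominator of the price and affordability results could be read as 15 stores or as 19 communities.

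**Working it through.** **Inputs.** Audited remote stores: 15 (Methods). Claimed stores: 19 of 46 (Strengths and Limitations). Communities: 19 (Setting and Recruitment). Comparator sites: 6 regional towns and Perth (Methods). The study is descriptive, so this is a reconciliation of counts and no sample-size formula applies.

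**Step 1: can 19 stores be obtained from the Methods?**
- Remote stores alone: 15.
- Remote stores plus towns: 15 + 6 = 21.
- Remote stores plus towns plus Perth: 15 + 6 + 1 = 22.

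None gives 19. Two explanations remain. Either the Discussion used the number of communities as the number of stores, or 19 counts all stores in these communities and only 15 of them are *independent*. The article supports neither explicitly. Under the second, the Discussion still claims more stores than the Methods audit, and four stores go unaudited without a stated reason.

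**Step 2: coverage.**
- As claimed: 19/46 = 41.3%.
- On the Methods count: 15/46 = 32.6%.
- Difference: 4/46 = 8.7 percentage points.

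**Step 3: communities without an audited store.** Each store lies in one community, so 15 stores can sit in at most 15 communities (15/19 = 78.9%). At least 19 − 15 = 4 communities (4/19 = 21.1%) contain none, and more than 4 if any community holds two of the stores. For these, the community-store term in the promised three-level comparison is undefined.

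**Step 4: does progress to date settle the count?** The Results section reports 10 communities accessed and prices from 8 remote stores analyzed. Simple scaling gives 8/10 × 19 = 15.2. This is compatible with 15 but does not confirm it: the figure counts stores analyzed, analysis may lag behind visits, and the first 10 communities are not a random sample of the 19.

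**Step 5: what if the gap were filled with town prices?** A community assigned the prices of its nearest town has a ratio to that town of 1.0 by construction. As an assumption for illustration only, let audited remote stores be 1.2 to 1.5 times the town price, with 15 such stores and 4 communities set to 1.0:
- Lower end: (15 × 1.2 + 4 × 1.0)/19 = 22/19 = 1.16.
- Upper end: (15 × 1.5 + 4 × 1.0)/19 = 26.5/19 = 1.39.

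Pooling in this way would shrink the remote price gap without any new information about remote prices.

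**The case against.** The strongest reply is that this is a reporting slip. The 19-of-46 figure appears only as a strength in the Discussion, no estimator uses it, and the Methods state 15 openly. The Abstract treats the store as the audited unit. Fifteen stores spread over 19 communities can loosely be called audits across them. The nearest towns are audited too, and the Introduction says residents without a store shop in a regional town, so the prices they pay may already be collected. Linking each such community to its retailer is detail that a condensed article may leave to the full protocol.

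Part of this stands. A reader might infer that at least four communities are left out of the price benchmark, that they have the worst food access, and that the burden is therefore understated. The article does not support that chain. No passage excludes a community. Having no audited store is not the same as having no store, because *independent* is undefined and the community may have another store or share one. The Introduction describes long travel but does not rank access. Travel is also not among the external-audit outcomes, and on the planned price outcomes, adding these communities at town prices would make the gap look smaller, not larger.

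What does not stand is that nothing needs correcting. The two store counts conflict in the current text, and leaving detail to a fuller document does not explain a contradiction. The towns are audited as comparators, which does not supply the community-store term of the comparison.

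**Conclusion.** The concern holds as a contradiction in the store count and an undefined comparison. The Methods give 15 stores and the Discussion 19, and nothing in the article reconciles them. If 15 is right, coverage is 33% and not 41%, and at least 4 of 19 communities (21%) have no audited store to compare with town and capital.

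The conflict between the counts rests on no assumption. The figures of 33% and 21% depend on 15 being the correct count, and the second also on each store being located in a single community. Why these communities lack an audited store is not stated, so neither the presence nor the direction of a bias in the price results can be inferred.

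**What to change.** 1. Reconcile the Abstract, the Methods and Strengths and Limitations to one store count. If it is 15, state coverage as 15 of the 46 very remote stores (33%) and give n=15 for all store outcomes. If it is 19, correct the Methods.
2. Define *independent*, and say whether any store in the 19 communities falls outside the term.
3. Limit the store-versus-town and store-versus-capital benchmark (objective 2) to communities with an audited store, and give that number.
4. List the other communities in a separate table, each with the audited retailer its residents use. Do not pool them into the remote-store mean at town prices. Say in the feedback to those communities that no local store comparison is available.

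The cost is a smaller stated coverage figure and a short table. The local environmental health practitioners, whom the article describes as knowing the communities well, could name the retailer. No further store audit is needed where that retailer is already in the survey. The correction should be made before any community or policy report quotes the coverage.
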